### Patient follow up

Prior to starting the study the length of stay on each of the surgical wards was obtained and was shown to be an average 4 days. Therefore it is also necessary to capture data regarding any surgical site infections post discharge. On discharge from the study ward each patient receives a letter and a questionnaire to be completed by their general practitioner (GP) in the event that they visit their GP for treatment of their surgical site wound. The questionnaire collects follow up information on whether any antibiotics have been prescribed by the GP and the state of the surgical site wound. In addition, the consultants who review the patient in outpatients are asked to complete the same questionnaire if they identify a surgical site infection.

### Patient information and communication

Upon admission to a study ward all patients receive an information leaflet about the study; detailing what MRSA is, why it is important to screen for MRSA and why we are undertaking the study. A research nurse is available to provide further information and answer questions. If a patient is found to be MRSA positive during their stay they are given a second information leaflet answering a number of questions regarding colonisation with MRSA, and in addition they receive a third information sheet on the correct use of the decolonisation treatment. Upon discharge from the ward each patient receives a final information sheet as well as a questionnaire to be completed by their GP following any visit regarding their surgical site. For short stay patients who are discharged before their admission result is available, a letter is sent to them at home informing them that MRSA had been isolated from a screening sample. This is accompanied by an information sheet with contact details for a research nurse they were able to phone for information and reassurance regarding the MRSA. If the patient is discharged to a nursing home the community infection control nurses is contacted and liaises with the nursing home.

### Implementation of infection control measures

The infection control procedures implemented are standardised across all wards regardless of the method of testing for MRSA. Upon identification of a patient being colonised with MRSA the result is telephoned to the ward. If space is available, the patient will be placed in a side room on the ward. If a side room is not available, or if the patient needs to be observed, the individual will nursed on the open ward. When operationally possible wards with several patients colonised with MRSA will nurse these patients together in one bay (cohort nursing) and dedicate a specific nurse to care for the patients. For all these patients an isolation precautions barrier sign (yellow and black) is placed by the bed side; gloves, aprons and alcohol gel are placed at the end of the bed and the patient is commenced on decolonisation treatment. Decolonisation treatment consists of five days of aquasept skin wash, containing triclosan and mupirocin nasal cream, followed by two days of no treatment and then re-screening of the patient. For patients who have strains that are resistant to mupirocin, Polyfax, containing polymyxin B and bacitracin, is used as the alternative. Additionally all patients who are colonised with MRSA receive a surgical review, this is aimed at establishing whether the surgical procedure is necessary immediately or can be delayed. In the former case the surgical prophylaxis is changed to teicoplanin (standard prophylaxis is cefuroxime and metronidazole), but if it is possible to delay surgery the patient undergoes a course of decolonisation treatment as detailed above, either at home or within the hospital.

The implementation of all infection control measures is audited within 12 hours of a patient being identified as being colonised with MRSA followed by continuous monitoring during their admission by the study research nurses. All measures are documented, and any failures to comply with these are both documented and rectified.

### Data collection

A comprehensive data set is being collected on all study patients. Data is entered directly by the research nurses onto laptops on the wards using a specifically modified Access database and then uploaded onto a secure server. Information collected includes patient ID, demographic data, risk factors, antibiotic usage, bed movements, length of stay, and treatment outcomes. For patients who are colonised with MRSA additional information is collected regarding implementation of infection control measures and decolonisation treatment.

Laboratory data collated includes patient ID, date and time sample taken and received by lab, and the IDI_MRSA and culture results.

### Data analyses

Analysis will be based on all individuals presenting for admission to the 7 surgical wards (intention to treat), including emergency and planned admissions. Numerical and graphical summaries of all the data will be compiled, including a detailed description of missing data at the ward and individual level.

Sensitivity and specificity will be estimated for PCR and culture tests. Receiver operating characteristic (ROC) curves are not appropriate because this is not a quantitative test. However, the positive predictive value (PPV) and negative predictive value (NPV) will be calculated. We will examine test replicability (i.e. precision) which reflects the variance in a test result that occurs when the test is repeated on the same specimen. Test reliability (e.g. failure rates) and laboratory turn-around time will also be compared.

The main clinical outcome measures will be MRSA cross-transmission rates, antibiotic therapy and MRSA-related morbidity. Secondary outcome measures will include length of in-patient stay, ITU episodes, a final outcome recorded at discharge, and MRSA infection at the outpatient follow-up clinic. Measures of resource use will include the cost of hospital episode and any re-admissions for MRSA.

The numbers of patients becoming infected, the cross-transmission rates and the numbers of MRSA-related deaths within each ward will be compared for the molecular and technical periods. The main analysis will focus on ward by period level data summaries. It seems likely that the number of new MRSA cases observed in each ward in each period will follow a Poisson distribution with mean depending on the size and type of the ward and whether the molecular or technical testing is being used in that period. A non-linear repeated measures random-effects analysis will be used to compare the mean number of cases, rate of cross-infection and number of MRSA related deaths. Ward by period interaction-level covariates could be included in this analysis. Depending on the observed rate of MRSA colonisation or infection and admission to the different wards, a normal approximation to the Poisson distribution may be appropriate, enabling linear modelling techniques to be used.

Further analyses will use linear or non-linear mixed effect models to assess the effects patient-level covariates. Estimates of the difference between the molecular and technical periods adjusted for the effect of covariates will be obtained.

Health service resource use will similarly be compared.

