## Methods/Design

### Study Setting and Population

The study is set in a large teaching hospital with over 1,200 beds, providing services to a large population with a wide range of socio-economic, ethnic and age characteristics. All patients admitted to the 7 surgical wards are included in the study. The seven wards include general surgery (2), vascular (1), thoracic (1), ENT (1), trauma and orthopaedics (2) and urology (1). The total capacity of the wards ranges between 20 and 34 beds, and in total is 195 beds; with an average length of stay on the wards of 4.5 days. All of the wards have a limited number of single rooms (2 – 5), none of which have ensuite facilities.

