### Sampling

The study design uses only nasal samples for MRSA screening, for several reasons. Firstly, and most importantly, at the start of the study all published work evaluating the IDI-MRSA assay had used only nasal samples [11]. Secondly a nasal sample is easily obtainable for large scale screening, ensuring comprehensive coverage. Additionally, in previous studies nasal samples have been shown to have a high sensitivity (84%) [16]. Screening swabs are taken from all patients on admission and then if the sample is negative the patient is screened every four days until discharge, and upon the day of discharge. Regular sampling at 4 daily intervals enables the implementation of infection control procedures in a timely manner and the detection of cross infection. Additional samples, for example blood cultures and wound swabs are sent on clinical suspicion as is normal hospital policy.

All samples from the molecular wards are collected by a research nurse at 8 am and 2 pm, Monday to Friday and once daily at 1 pm on a Saturday and Sunday. Samples from the technical wards are transported to the laboratory using the hospital portering service which operates during the day 7 days a week.

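### Cross-infection is modelled as observed cases among all admissions, with no denominator for patients at risk or time under swab observation, so a swabbing difference that follows the test could bias the primary comparison

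*Protocol article*

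**What the plan says.** All references are to the Protocol article.

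- **Population (Data analyses).** "Analysis will be based on all individuals presenting for admission to the 7 surgical wards (intention to treat), including emergency and planned admissions". No narrower set is named for cross-infection.
- **Modelled quantity (Data analyses).** The main analysis uses ward-by-period summaries under this assumption: "the number of new MRSA cases observed in each ward in each period will follow a Poisson distribution with mean depending on the size and" (cut here). The other terms named for the mean are the kind of ward and which test is in use. A cross-infection rate is also to be compared, but this section gives no denominator for it. Missing data are to be described; nothing links them to the outcome.
- **How acquisition is seen (Sampling).** "Screening swabs are taken from all patients on admission and then if the sample is negative the patient is screened every four days until discharge", with a further swab scheduled on the discharge day. The purpose is stated: "Regular sampling at 4 daily intervals enables the implementation of infection control procedures in a timely manner and the detection of cross infection". Blood cultures and wound swabs are added on clinical suspicion.
- **Length of stay.** Study Setting and Population has "with an average length of stay on the wards of 4.5 days"; Patient follow up says "the length of stay on each of the surgical wards was obtained and was shown to be an average 4 days".
- **Handling by arm (Sampling).** "All samples from the molecular wards are collected by a research nurse at 8 am and 2 pm, Monday to Friday"; weekend collection is once a day. For the other arm: "Samples from the technical wards are transported to the laboratory using the hospital portering service", during the day on all seven days. Under Overall study design and approach, results return within 2 hours of receipt on molecular wards and within 2 days on technical wards.

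**The concern.** A silent acquisition becomes a case only if the patient was negative on admission and has a later swab. With a four-day interval and a mean stay of about the same length, many patients have the discharge-day swab as their only second look. If it is missed through early discharge, transfer, death or oversight, the patient's status is unknown. That patient still belongs to the analysed population and adds nothing to the observed count, which in the model has the same effect as being uninfected.

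This would be harmless to the ratio if later swabs were equally complete under both tests. Two features give reason to check. Collection routes differ by arm, and so does the time at which a patient's negative status, which triggers four-daily re-screening, becomes known. Both features move with the test when wards switch, so any swabbing gap they cause would not cancel in the cross-over. At stake is the primary outcome: better later swabbing on molecular wards would hide a benefit of rapid testing, and worse swabbing would create or exaggerate one.

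**Working it through.** **Inputs from the documents (Sample size):** 10,000 patients, taken as 5,000 per arm; 5% colonised on admission; transmission rate 0.5 (technical) and 0.3 (molecular); stated power 90%. Alpha and sidedness are not given; 0.05 two-sided is assumed.

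**Step 1: the plan's own figure.**
- Expected cases: 5,000 × 0.05 × 0.5 = 125 and 5,000 × 0.05 × 0.3 = 75, a ratio of 0.60.
- Normal approximation with null variance 2 × 125: Φ((50 − 1.96 × √250)/√200) = Φ(1.34) = 0.911. With variance 125 + 75 it is 0.942.
- The stated 90% is reproduced, on the footing that every acquisition is observed.
- The transmission rate here is 125/250, cases per colonised admission. It too has no term for whether acquisition could be seen.

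**Step 2: incomplete later swabbing.** Let c be the share of acquisitions with a swab after they occur, approximated by completion of any later swab. Then observed ratio = true ratio × c(molecular)/c(technical). The documents give no completion figures, so every pair below is an assumption.

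| Any later swab, molecular v technical | True 1.0 seen as | True 0.60 seen as |
|---|---|---|
| 85% v 75% | 0.85/0.75 = 1.13 | 0.68 |
| 80% v 65% | 0.80/0.65 = 1.23 | 0.74 |
| 90% v 70% | 0.90/0.70 = 1.29 | 0.77 |

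Reversing a pair inverts the factor: 80% molecular v 90% technical gives 100/112.5 = 0.89 with no true effect.

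**Step 3: error rates, with the simple Poisson comparison of the plan's power calculation (no ward clustering).**
- No true effect, 90% v 80% in either direction: 112.5 v 100 expected cases, z = 12.5/√212.5 = 0.86, rejection probability 13.8% instead of 5%. For 90% v 70%: 112.5 v 87.5, rejection 42.4%.
- Planned effect, molecular 90% v technical 80%: 67.5 v 100, ratio 0.675, power 64% (null variance) to 71% (variance of the sum). A log rate ratio with swabbed patients as denominator has 90%, if missing swabs are unrelated to acquisition.
- Equal 80% completion leaves the ratio at 0.60, with power 83% to 89%.

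**Step 4: only discharge swabs missed.** Assume an exponential stay with mean 4.5 days, constant low hazard, persistent carriage and complete four-day swabs. With q = exp(−4/4.5) = 0.411, the share of acquisitions caught at a four-day swab is (4/4.5) × q/(1 − q) = 0.62. The other 0.38 depends on the discharge swab. Observed ratio when the true ratio is 1.0:
- 85% v 75%: (0.62 + 0.38 × 0.85)/(0.62 + 0.38 × 0.75) = 1.04
- 80% v 65%: 1.07
- 90% v 70%: 1.09

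The stay distribution is not given, so the 0.62 is itself assumption-bound.

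**The case against.** The strongest reply is that the article states no error. It nowhere says that unswabbed patients are uninfected; the intention-to-treat sentence is general; and risk sets, offsets and handling of missing swabs are often left to a fuller document. Part of this stands: a reader might infer an explicit rule that missing means negative, and there is none. But the article does fix the population and the modelled quantity, and following both has that effect. Ward size in the Poisson mean does not supply patient-days under observation.

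Second, a discharge swab is scheduled for every admission-negative patient, so the problem needs missed swabs, which the article does not report. This stands. A reader might also infer that swabbing did differ between arms. The text does not support that: Sampling describes who collects or transports samples, not who takes them, and infection control is standardised across wards.

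Third, every ward serves under both tests, so stable ward differences in swabbing largely cancel. This stands too; only a gap tied to the test remains.

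Fourth, clinical samples and outpatient follow-up can reveal infection without a screening swab. That is correct, so the point is confined to silent acquisition.

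Fifth, it is tempting to read the 1.13 to 1.29 range as the effect of poor discharge swabbing. It applies to completion of any later swab; Step 4 shows the smaller figure for discharge swabs alone. Nor does including admission-positive patients bias the ratio by itself: at an equal 5% in both arms it is unchanged.

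Last, restricting to re-swabbed patients conditions on something that happens after allocation. This is a real cost, and the fix has to carry it openly.

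**Conclusion.** The point holds as a weakness in how the primary comparison is specified. An all-admissions population with observed counts and no at-risk or swab-time denominator lets any test-linked difference in later swabbing enter the estimated effect of the test, in either direction. Describing missing data would expose such a gap but would not change the estimate.

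The size cannot be fixed from the documents. Under the assumed completion pairs the ratio is distorted by 13% to 29% if any later swab may be missing, and by about 4% to 9% if only discharge swabs are. The first range treats missing swabs as unrelated to acquisition; the second rests on the exponential-stay model. Both assume that the whole gap follows the test. The change is worth making before analysis because the data needed are already collected; it is not evidence that the trial's result is biased.

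**What to change.** 1. Keep all admissions for the clinical, length-of-stay and cost outcomes.
2. For cross-infection, analyse patients negative on the admission swab, with a Poisson offset for patient-days from that swab to the last swab or first positive.
3. Judge admission status and acquisition by the same method in both arms. Direct culture is done on all wards. Results found only by broth enrichment or by the extra incubation of discrepant plates should be set aside here, because those steps depend on a PCR result and so arise only on molecular wards.
4. Tabulate completion of any later swab, and of the discharge swab, by ward, period and arm.
5. Add a sensitivity analysis that imputes unswabbed stays from swabbed stays of the same ward, period and length.
6. Report the all-admissions result alongside.

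**Cost.** Analysis wording and some programming; sample dates and times, PCR and culture results and length of stay are already recorded (Data collection). The downside to state is that stays without a second swab leave the main rate. This may select longer stays and is unbiased only if missing swabs are unrelated to acquisition, which is why items 4 to 6 belong with it.

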### Sample size

Given the limitations on published data available to inform the sample size estimate at the outset of the study, it was decided, in the light of operational constraints, to monitor MRSA colonisation and infection rates in seven wards for eighteen months, with a cross-over from molecular to technical testing or vice versa after nine months. Admission rates to the wards led to an estimated total of 10,000 patients being included in the study, with 5000 being assigned to each of the two periods.

Assuming that 5% of patients are MRSA colonised on admission to the wards, with a transmission rate in the technical wards of 0.5, a total of 125 new cases of infection in the control arm would be expected.

The power of the study can be calculated assuming that the number of new cases follows a Poisson distribution and using the normal approximation to the Poisson. If, for the purpose of the power calculation, it is assumed that admission rates and MRSA colonisation rates on admission are the same for all seven wards and in both periods, and that and MRSA transmission rates are the same for all wards using molecular or technical testing, a total of 10,000 admitted patients would mean that the study had 90% power to detect a reduction in the transmission rate from 0.5 to 0.3, corresponding to a drop in the expected number of new cases in the molecular wards from 125 to 75.

### Economic analysis

MRSA transmission may have a range of direct cost consequences to healthcare. The costing study will estimate differences in the cost of resources used in the molecular and technical wards. The economic analysis will compare resource use (costs) with any measurable changes in health outcomes (benefits). The health outcomes (or endpoints) will be measured in terms of changes in MRSA transmission and subsequent health outcomes. Any uncertainties in the cost and outcomes data will be incorporated into a sensitivity analysis.

The cost of each test will be determined through observation in the laboratory, once the learning curve is over and routine use of the technology is established. Maximum throughput for each method will be estimated. Test costs will include: labour (skill levels will be assessed for particular tasks); consumables; capital (converted into an annual equivalent cost and apportioned to tests based on annual throughput); maintenance costs; and overheads.

In both types of ward, other NHS costs related to patient care will be estimated. These will include resources associated with length of stay/ITU episodes, prescribing costs, and for MRSA positives post discharge care costs, including subsequent admissions for MRSA. Costs of any other relevant treatment will also be recorded. The use of services will be costed from a variety of sources, including the finance departments of the hospital and national sources [21]. Hospital notes and records will also be audited for information on service use.

The appropriate technique of economic evaluation will depend on the results of the study [22]. The simplest eventuality would be where the least expensive intervention is found to be better on at least one outcome measure and no worse on any other i.e. dominant. Another is where two interventions have the *same *outcomes (e.g. MRSA cross-infection rates), in which case the economic evaluation required when comparing the two is a cost-minimisation analysis. However, where an intervention is clearly better in terms of outcome but also more costly, a different approach is required. One accepted method is to compare the different interventions in terms of a single outcome measure identified as clinically important. The primary outcome measure meets this requirement. Therefore, the cost per unit improvement in MRSA transmission rate will be used to provide an estimate of overall cost-effectiveness of a screening strategy for MRSA in surgical patients using rapid IDI tests and infection control strategies.

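### The form of economic evaluation is chosen after the results are seen, and the cost-minimisation branch has no equivalence margin, so an imprecise but real benefit could be counted as zero

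*Protocol article*

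**What the plan says.** The Economic analysis section of the protocol article makes the method conditional on the findings: "The appropriate technique of economic evaluation will depend on the results of the study". It then describes three situations.

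- **Dominance.** The cheaper strategy is better on at least one outcome and worse on none.
- **Same outcomes**, with cross-infection rates as the example, "in which case the economic evaluation required when comparing the two is a cost-minimisation analysis".
- **Better but dearer.** The text says that "where an intervention is clearly better in terms of outcome but also more costly, a different approach is required", and that "the cost per unit improvement in MRSA transmission rate will be used to provide an estimate of overall cost-effectiveness".

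The same section promises that "Any uncertainties in the cost and outcomes data will be incorporated into a sensitivity analysis". Among the costs it lists, "for MRSA positives post discharge care costs, including subsequent admissions for MRSA" are to be estimated.

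The Sample size section expects "an estimated total of 10,000 patients being included in the study, with 5000 being assigned to each of the two periods". It claims 90% power for a fall in the transmission rate from 0.5 to 0.3, that is, from 125 to 75 new cases. The article gives no equivalence or non-inferiority margin.

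**The concern.** Two observed rates will almost never be identical, so someone must judge whether they are the 'same' after seeing the data. The article does not say how. A study sized to show a reduction does not show equality when it fails to show that reduction. Cost-minimisation nevertheless takes the effect difference as zero and compares costs alone. No branch covers the awkward middle case, in which the estimate favours one test but its interval includes no difference.

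If the cost-minimisation branch were taken in that case, rapid testing would be judged on cost without credit for cases it may have averted. Aim 3 in the Background promises an assessment of cost-effectiveness.

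The secondary concern is the costing group. Follow-up costs attach to MRSA positives, and the Laboratory protocols section describes unequal detection. Molecular-ward swabs get PCR and direct culture, with longer incubation for discrepant results and broth enrichment for PCR positives. Technical-ward swabs get direct culture only. The same section concedes that direct culture is not the most sensitive method. The two arms may therefore send different fractions of their true carriers into the post-discharge costing.

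**Working it through.** **Inputs from the Sample size section.** "Assuming that 5% of patients are MRSA colonised on admission to the wards, with a transmission rate in the technical wards of 0.5". There are 10,000 admissions. With equal admission rates across wards and periods, as that section assumes, each testing method covers about 5,000. Counts are Poisson with a normal approximation. Significance level and sidedness are not stated; two-sided 5% is assumed here.

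**Expected counts.** 5,000 × 0.05 × 0.5 = 125 and 5,000 × 0.05 × 0.3 = 75, as stated.

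**Reproducing the 90% power.**
- Null variance at the control rate: Φ((50 − 1.96√250)/√200) = Φ(1.34) = 0.911.
- Variance from both means: Φ(50/√200 − 1.96) = Φ(1.58) = 0.942.

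The first is close to the stated 90%. At the design effect, the chance of a non-significant result is therefore 1 − 0.942 = 6% to 1 − 0.911 = 9%.

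**Smaller true reductions (assumed; the article gives none).** P(non-significant) = 1 − Φ((125 − m)/√(k(125 + m)) − 1.96), where m is the expected count under rapid testing. k = 1 is pure Poisson. k = 2 doubles the variance for between-ward variation, for which the article gives no figure.

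| True reduction | m | Cases averted | k = 1 | k = 2 |
|---|---|---|---|---|
| 40% (design) | 75 | 50 | 0.058 | 0.295 |
| 30% | 87.5 | 37.5 | 0.270 | 0.556 |
| 20% | 100 | 25 | 0.615 | 0.783 |
| 10% | 112.5 | 12.5 | 0.875 | 0.917 |

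**What an imprecise result looks like.** Suppose 125 v 100 were observed.
- Difference: 25 ± 1.96√225 = 25 ± 29.4, from 54 cases averted to 4 extra; p = 0.096.
- Rate ratio: 0.80, with SE(log) = √(1/125 + 1/100) = 0.134, giving a 95% CI of 0.62 to 1.04.

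These are Poisson intervals; ward variation would widen them. The result is neither 'same' nor 'clearly better', and the plan has no branch for it.

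**Costing group.** True carriers on admission per method: 5,000 × 0.05 = 250. The Background reports PCR sensitivity of 91.7% from an early evaluation, so 250 × 0.917 = 229 would be detected. Culture sensitivity is assumed.
- 90%: 225 detected; 229.25/225 = 1.02, an excess of 2%.
- 80%: 200 detected; 229.25/200 = 1.15, an excess of 15%.
- 70%: 175 detected; 229.25/175 = 1.31, an excess of 31%.

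These are excess patients entering the costing, not excess cost.

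**The case against.** The article never says that 'same' means non-significant and names no P value. Its three situations read as illustrations, and a fuller economic plan may define the terms. The section also says that costs will be set against measurable changes in health outcomes and that uncertainty goes into a sensitivity analysis. Aim 3 and the Modelling section add further evaluation of policies. At the planned effect the study would usually reach significance. The larger percentages above need smaller effects that the article does not mention.

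Much of this stands. A reader might infer that a non-significant result is likely; the study's own power contradicts that at the design effect. A reader might also infer that the plan equates non-significance with equality. That is a natural reading, but only an inference. Nor do the documents show that an adoption decision would reverse, since they contain no cost figures.

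On the effect measure, one unit of transmission rate is twice the assumed control rate of 0.5. That is only scaling: cost per 0.1 or per 1.0 carries the same information.

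On the costing group, MRSA positives might mean culture-confirmed patients, in which case much of the gap could close. An extra detected carrier adds cost only by using services. The Data analyses section lists MRSA re-admissions without restricting them to screen positives, and every discharged patient receives the questionnaire for the general practitioner.

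The objection does not remove the main point. Choosing the method from the results is what the article says, not a detail it leaves out. A general sensitivity analysis does not clearly keep the joint uncertainty in cost and effect once the effect has been set to zero.

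**Conclusion.** The concern holds in a limited form. The technique depends on the results, cost-minimisation is named for outcomes that are the 'same', there is no margin, and the study is sized for superiority. Treating a real but imprecise benefit as zero is therefore a risk of the rule, not a stated or expected consequence.

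If non-significance were used as the trigger, the risk is about 6–9% at the design effect, and about 27%, 62% and 87% at assumed true reductions of 30%, 20% and 10%. With the variance doubled for wards (assumed), it is about 30% at the design effect and 56% at a 30% reduction. All of these figures assume a two-sided 5% test.

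The costing-group point is secondary. The unequal detection procedures are in the text, but the size and direction of any effect on the incremental cost are unknown. The 2% to 31% range rests on assumed culture sensitivity and counts patients, so no single percentage should be read as a cost bias.

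**What to change.** 1. Delete the cost-minimisation branch. Before analysis, commit to one cost-effectiveness analysis whatever the primary result shows.
2. Report incremental cost and incremental MRSA acquisitions averted. Count acquisitions by direct culture, which is done in both arms, leaving out results from the extra incubation and broth steps used only on molecular wards.
3. Estimate the joint uncertainty in cost and effect with a method that allows for wards, and show it as net benefit or an acceptability curve over a range of values per acquisition averted.
4. Define MRSA positives for post-discharge costing by a method common to both arms: direct culture, or clinical samples, which the Sampling section says follow normal hospital policy. Alternatively, compare readmission costs for all admitted patients.

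The cost is a change of wording and modest extra analysis. Hospital records are already to be audited for service use. The Discussion says recruitment is only now being completed, so the rule could still be fixed before analysis.
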